## Methods

### Trial Design

The trial employs a between-subjects single-message factorial design in which the independent variables of interest are systematically manipulated. This is done using the video vignette methodology. In experiment 1, hematologists’ information structuring and expressions of caring are varied in a 2 (standard versus enhanced structuring) × 2 (standard versus enhanced caring) design. In experiment 2, hematologists’ information tailoring and expressions of caring are varied in a 2 (high versus low need for information) × 2 (high versus low amount of information provided) × 2 (standard versus enhanced caring) design. This results in 12 experimental conditions, or interventions, across the trial (see Tables 1 and 2).

**Table 1 table1:** Experiment 1: Manipulation of provider information structuring and caring (2×2 design).

Manipulations	Standard of care	Caring
Standard of care	Standard of care	Enhanced caring
Structuring	Enhanced structuring	Enhanced caring and structuring

**Table 2 table2:** Experiment 2: Manipulation of provider caring and information tailoring in a match/mismatch design (2×2×2 design).

Manipulations		Provider			
		Enhanced caring		No caring	
		Additional information provision	No additional information provision	Additional information provision	No additional information provision

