##### Tailoring

Patients’ need for information was operationalized in the video script by having the patient respond to a prompt by the physician (eg, “Would you like to know more about this?”). The patient either confirmed a preference for more information (eg, “I would like to know as much as possible”) or stated that the information received was considered sufficient for the time being (eg, “It’s clear for now. I would like to let it all sink in”). This was done twice, once at the beginning and once toward the end of the consultation, keeping the patient’s need for information (high vs low) consistent across the script. Tailoring was defined as a match between a high information need of the patient and the provision of further information (*tailoring*^*+*
^) or a match between a low-information need of the patient and the absence of further information provision (*tailoring*^*−*
^). In contrast, lack of tailoring was defined as a mismatch between need for information and information provision (*no tailoring*^*+*
^ and *no tailoring*^*−*
^; see Table 2).

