### Analysis

Data will be cleaned in a stepwise procedure [76], including the identification of missing values because of dropout, standardization and normalization of data, and outlier analysis. Data will subsequently be analyzed using IBM SPSS statistical package. In the first step, it will be determined whether the experimental groups, within each of the 2 subexperiments of the trial, are indeed comparable in terms of participant characteristics, such as sociodemographics, personality traits, and disease history. If differences are found, these will be controlled for in subsequent analyses. Then, for each of the 2 experiments, one-way analysis of variance or covariance (when aspects need to be controlled for) will be conducted to test the effects of information structuring, information tailoring, and caring on information recall, satisfaction, and trust (H1, H2, and H3, respectively). Additionally, the interaction effect between caring and information structuring as well as tailoring will be added to these models (RQ1). It will be investigated to what extent patient characteristics moderate the hypothesized relationships (RQ3). If necessary, because of violations of the assumption of homogeneity of variance, Welch F statistic will be employed. Posthoc comparisons, using Bonferroni or Games-Howell, will be used as applicable, to create a better understanding of between-group differences. Finally, linear regression analyses will be used to assess possible relationships of information recall, satisfaction, and trust with expected symptom distress (RQ2). Significance levels are determined at *P*<.05.

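### The Analysis section names a one-way ANOVA for 2×2 and 2×2×2 factorial designs and then adds interactions that a one-way model cannot contain

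*Protocol article*

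**What the plan says.** The Trial Design section of the protocol article sets two crossed designs. Experiment 1 is "varied in a 2 (standard versus enhanced structuring) × 2 (standard versus enhanced caring) design". Experiment 2 is a "2 (high versus low need for information) × 2 (high versus low amount of information provided) × 2 (standard versus enhanced caring) design".

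The Tailoring subsection and Table 2 define tailoring through two of those factors: "Tailoring was defined as a match between a high information need of the patient and the provision of further information", or between a low need and no further information. A mismatch in either direction counts as lack of tailoring.

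The Analysis section then states, for each experiment, that "one-way analysis of variance or covariance (when aspects need to be controlled for) will be conducted to test the effects of information structuring", tailoring and caring on recall, satisfaction and trust, tied to H1, H2 and H3. It continues that "the interaction effect between caring and information structuring as well as tailoring will be added to these models (RQ1"). For unequal variances it says that "Welch F statistic will be employed", and it offers Bonferroni or Games-Howell post hoc comparisons.

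The Sample Size section gives 180 for structuring and 240 for tailoring, at alpha .05, power .80 and effect sizes of .10 to .25. It does not name the effect-size index.

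**The concern.** A one-way analysis has a single grouping factor, so no interaction can be added to it. The sentence on RQ1 therefore asks for a term that the model named just before it cannot hold, and neither fits the crossed designs. The reader must guess which part of the paragraph governs, and the possible readings give different tests.

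- **Cells as the factor (4 or 8 groups).** The test is an omnibus with 3 or 7 df. It rejects for any difference among cells, so rejection does not support H1, H2 or H3 in particular. This matters most for recall in experiment 2, where half of the vignettes give additional information and an effect of amount alone is plausible. The Discussion itself concedes that differences in vignette duration might explain differences in outcome.
- **Each two-level factor in turn.** The tests do address H1 to H3 as marginal effects, but the model still has no place for RQ1.

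The coding of tailoring adds to the ambiguity. By the protocol's definition tailoring is the need × amount interaction, so tailoring × caring is a three-way interaction. The Analysis section names tailoring and its interaction with caring, but does not say how tailoring enters the model and lists neither need nor amount as a term.

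The Welch F fallback also belongs to a single grouping factor. It does not carry over to a factorial or covariate-adjusted model. The paragraph governs every primary hypothesis.

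**Working it through.** **Inputs.** Alpha .05, power .80, N = 180 and 240, effect size up to .25 (Sample Size section); 4 and 8 cells (Trial Design section). Assumptions: the index is Cohen's f, cells are equal within each experiment, and N is as planned.

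**Formula.** With k cells and a test on df1 degrees of freedom, λ = N·f² and power = P[F′(df1, N − k, λ) > F(.95; df1, N − k)].

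**1. The plan's own figures.** One-way omnibus at f = .25:
- 4 cells, df1 = 3: the smallest N is 179, or 180 with equal cells. At N = 180, λ = 180 × .0625 = 11.25, critical F(3, 176) = 2.656, power .804.
- 8 cells, df1 = 7: the smallest N is 237, or 240 with equal cells. At N = 240, λ = 240 × .0625 = 15, critical F(7, 232) = 2.049, power .807.

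Both stated sizes are reproduced by one effect size.

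**2. Is that the only route?** No. A 1-df factorial test needs 128 at f = .25, but 180 at f = .21. It needs 245 at f = .18 and 220 at f = .19, so 240 corresponds to about .18. These values lie inside the stated range. The omnibus route is simpler because a single f gives both sizes, but it remains an inference.

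**3. Cells as the factor.** λ is the same whichever term produces the differences.
- Experiment 1, caring effect only (f = .25), no structuring effect: the 4-cell test rejects in 80.4% of trials.
- Experiment 2, amount effect only (f = .25), no tailoring or caring effect: the 8-cell test rejects in 80.7%. A one-way test over the four need × amount groups rejects in 91.2%.

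Power for one true 1-df effect of f = .25:

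| | Omnibus over cells | 1-df contrast, factorial model |
|---|---|---|
| Experiment 1, N = 180 | .804 | .916 |
| Experiment 2, N = 240 | .807 | .971 |

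**4. Each two-level factor in turn.** Code need, amount and caring as ±1 and match = need × amount. The four matched cells contain two with additional information and two without, and so do the four mismatched cells. Over eight equal cells the products of match with need, amount and caring each sum to 0. Under a pure amount effect the noncentrality of the match contrast is therefore 0. In 20,000 simulated trials it rejected in 4.9% (factorial model) and 4.3% (one-way on match versus mismatch).

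The cost is that omitted factors stay in the error term: f_eff = f/√(1 + f_omitted²) = .25/√1.0625 = .2425. With one omitted factor of f = .25, power falls from .916 to .899 for structuring (N = 180) and from .971 to .963 for tailoring (N = 240).

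**5. RQ1.** Structuring × caring needs both factors in the model. Tailoring × caring equals match × caring = need × amount × caring. Neither exists in a model with one factor.

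**The case against.** The strongest reply is that one-way is only a wrong label. The paragraph lists structuring, tailoring and caring as the effects to be tested and maps them to H1, H2 and H3. It never says that the grouping factor is the 4 or 8 cells. Once the promised interactions are added, the model is factorial, and SPSS fits it routinely. A condensed article may leave the coding of terms to a fuller document. Post hoc comparisons are also planned, so an omnibus rejection need not be read as support for one hypothesis.

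Much of this stands, and it rules out four stronger readings that a reader might infer:

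- *Experiment 2 inevitably mixes tailoring with amount of information.* It does not. Under the protocol's match/mismatch definition and equal cells, amount is balanced across the contrast. Mixing arises only in a one-way test over the eight cells or the four need × amount groups.
- *H1 to H3 go untested.* Tests on each two-level factor do address them as marginal effects.
- *RQ1 is left out.* It is stated. The fault is that the named model cannot contain it.
- *The sample sizes can come only from omnibus tests.* The effect size is given as a range without an index, and 1-df tests at about .21 and .18 give the same sizes.

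What does not stand is that the label is harmless. It is the stated rule for the primary tests, and the Welch F and Games-Howell procedures also belong to a single grouping factor. With the cell-level match of 180 and 240, this makes a literal reading credible. The contradiction lies in the text itself, so it is not a detail left to another document.

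**Conclusion.** The contradiction holds. The named model fits neither the factorial designs nor the interaction sentence that follows it. How much this costs depends on which reading the analyst follows.

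Under the cell-level reading, which the sample sizes suggest but do not prove, the test isolates no hypothesis. The rejection rates of 80% and 81% become false support for H1 or H2 only if that omnibus result is taken as the test of the hypothesis, which no section says outright. The certain loss on this reading is power: .80 and .81 against .92 and .97 at f = .25.

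Under the factor-level reading, H1 to H3 are validly tested with a loss of one to two percentage points of power when one omitted factor has f = .25. RQ1 remains outside the model. Marked imbalance between cells after dropout would weaken the orthogonality on which this reading rests.

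All figures assume Cohen's f, equal cells within each experiment and the planned N. The 470 participants reported as randomized are not used.

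**What to change.** In the Analysis section, replace one-way by factorial ANOVA/ANCOVA and name the terms:

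- **Experiment 1:** structuring, caring and their interaction. H1 = structuring main effect; H3 = caring main effect; RQ1 = the interaction.
- **Experiment 2:** need, amount, caring and all interactions. H2 = need × amount, that is, match minus mismatch; H3 = caring main effect; RQ1 = need × amount × caring.

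Use ±1 (effect) coding and report each as a 1-df contrast with a confidence interval.

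In place of the one-way Welch F, name a variance-robust fallback that fits the factorial or covariate-adjusted model. Heteroscedasticity-consistent (HC3) standard errors are one option; the choice among such methods is a preference.

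Restate the power basis for the 1-df tests and name the effect-size index. At f = .25 the planned 180 and 240 are more than enough (.916 and .971). At the lower end of the stated range, f = .10, they give only .27 and .34, so the restated basis should say which effect the trial is sized for.

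The cost is a reworded analysis paragraph and a short power statement. No new data or software is needed. The Results section reports data collection as complete with analyses still to come, so the change should be dated and made before the results by condition are seen.

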## Results

Data collection has now been completed. A total of N=607 participants went to our homepage, provided informed consent online, and started the survey. A total of N=470 completed the first part of the survey and were randomized to receive 1 of the 12 video vignette interventions within 1 of the 2 experiments (77.4%, 470/607). Participants did not differ from those who dropped out, except for their age (in experiment 1, N=148): completers were younger (mean 3.8 years; *P*=.002) and consequently less likely to be retired (41.2%, 194/470) vs 56.4% (83/148; *P*=.006)*.* The first analyses will be available in Spring 2019.

## Discussion

### Strengths and Limitations

This study protocol describes the procedures for a randomized controlled trial in which 2 video vignette experiments are used to test the effects of physician information giving about side effects of cancer treatment on patient outcomes. Specifically, the effects of cognitive-oriented communication strategies (ie, information structuring and tailoring) as well as affect-oriented strategies (ie, caring) on patient recall, satisfaction, and trust are tested in conjunction. The outlined approach has both advantages and limitations.

Video vignette experiments allow researchers to experimentally test the causal relationships between communicative behaviors and consultation outcomes. This is particularly relevant when systematic manipulation of physicians’ behaviors is undesirable for ethical or practical reasons. This trial thus has the potential to yield critical evidence to support interventions to change communicative behaviors in clinical practice. In the preparatory phase of the trial, the video vignettes were carefully developed in a stepwise procedure, involving a panel of hematologists, patients with cancer, health communication researchers, and medical psychologists as well as a pilot test. Through this procedure, the script and its manipulations were thoroughly evaluated to ensure vignette realism as well as the effectiveness of the separate manipulations.

However, it should be noted that design artificiality can hamper ecological validity and that the use of analogue patients can hinder participants’ ability to identify with the portrayed clinical situation. To ensure vignette realism, the script was based on a transcript of a full-length hematology consultation. As such, the script sought to represent a true-to-life hematology consultation rather than an ideal situation. Duration differences between the different versions of vignettes might account for differences in outcomes rather than the manipulation. However, duration differences are characteristic for realistic consultations, and compensating for these differences by adding *fillers* to the script may produce its own, undesirable, effects [63].

The pilot study demonstrated that participants were indeed able to identify and engage with the video patient. Inclusion of study participants who have previous experience with oncology consultations is expected to further improve identification with the vignettes, although our research group previously found no difference in identification between patients with cancer and cancer naïve participants [63].

As participants will be recruited via a panel of (former) patients with cancer and their relatives, as well as via patient organizations, it should be taken into account that panel participants may not be fully representative of the patient population. However, this is not deemed problematic as we primarily aim to identify pathways underlying effective information giving rather than to generalize patient outcomes to the population. The use of participants with previous experience with cancer does raise ethical concerns, as participants may experience feelings of anxiousness or sadness as a result of viewing a video in which a cancer treatment plan is discussed. This was reviewed by the institutional ethics committee. Participants are extensively debriefed following the experiment to minimize any negative impact of study participation.

Finally, it should be noted that, although video vignettes provide an effective method to study communication effects among (oncology) patients and their relatives, sometimes the use of so-called analogue patients poses a challenge. When striving to test the effects of information tailoring, the communication in the scripted vignettes is tailored to the video-patient rather than to the study participant. This may have implications for the findings. Direct effects of tailoring on participants’ recall of information cannot be assumed. To overcome this issue, we added an item to the survey, assessing participants’ personal information preferences (amount). Consequently, we can control for this variable in our statistical models.

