##### Background Measures

Survey questions concerning participants’ sociodemographic background included gender, birth year, ethnicity, living situation, educational level, and occupational status. In addition, questions concerning participants’ health literacy [68], medical knowledge (general and lymphoma-specific), overall health (1 item), and cancer (treatment and family) history were included. Personality trait measures included the avoidance scale of the Impact of Event Scale (8 items, 4-point scale) [69] to assess the tendency to avoid cancer-related issues, the Trait Anxiety Inventory (20 items, 4-point scale) [70] for the assessment of generalized anxiety, the Threatening Medical Situations Inventory (TMSI-2, Monitoring scale) [71] to assess a monitoring coping style, and a single item assessing information preferences in medical consultations (5-point scale).

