### Sample Size

The required sample size is estimated at N=420 participants (*structuring* N=180 and *tailoring* N=240), based on *a priori* power analyses in G*Power [75] with the alpha set at .05, a probability level of .80, and estimated medium effect sizes of .10 to .25 for the dependent variables, that is, information recall, information satisfaction, and trust in the physician.

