### Allocation and Blinding

Participants are automatically and randomly assigned to 1 of 12 conditions, or interventions, (1:1 ratio) in either the structuring or the tailoring experiment. Allocation is achieved by computer-generated randomization. Participants are unaware to which condition, that is, intervention, they are assigned (blinded). Researchers are unaware, for the duration of the trial, to which condition participants are assigned.

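### Adjusting for the participant's own information preference does not fix tailoring to the video patient; the term that addresses it, amount × own preference, is not named

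*Protocol article*

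**What the plan says.** Experiment 2 is a "2 (high versus low need for information) × 2 (high versus low amount of information provided) × 2 (standard versus enhanced caring) design" (Trial Design). Under Experimental Manipulations, Tailoring, "lack of tailoring was defined as a mismatch between need for information and information provision", the need being the one voiced by the patient in the video. H2 states that tailoring improves recall, and the Introduction justifies this by the personal relevance of the information to the person receiving it.

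The Discussion (Strengths and Limitations) acknowledges that "the communication in the scripted vignettes is tailored to the video-patient rather than to the study participant" and that a direct effect on participants' recall therefore cannot be taken for granted. It then presents an added survey item as overcoming the issue: "Consequently, we can control for this variable in our statistical models". Background Measures lists that item with the personality trait measures as "a single item assessing information preferences in medical consultations (5-point scale").

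The Analysis section adjusts for participant characteristics only where the experimental groups turn out to differ. It adds a general step on moderation by patient characteristics (RQ3). Neither the Analysis section nor the list of research questions mentions the preference item or its interaction with the amount of information.

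**The concern.** The article identifies a validity problem for one of its main hypotheses, declares it solved, and names a device that cannot solve it. A covariate main effect shifts everyone with a given preference by the same amount, whatever video they saw. The open question is whether extra information helps participants who want it more than those who do not. That asks how the effect of amount changes with own preference, which is an interaction.

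At stake is interpretation. A reader told that H2 was adjusted for own preference may take the result as evidence on tailoring to the recipient, when it remains evidence on watching someone else being tailored to. The article intends its results to inform training of clinicians, so the distinction matters.

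**Working it through.** **1. The plan's own figure.** Sample Size states: "The required sample size is estimated at N=420 participants", 180 for structuring and 240 for tailoring, "with the alpha set at .05, a probability level of .80, and estimated medium effect sizes of .10 to .25". Taking the effect size as Cohen's f (the metric is not named), the omnibus F test has noncentrality λ = N·f². At f = .25:
- 4 cells, N = 180: λ = 180 × .0625 = 11.25, df 3 and 176, power .804.
- 8 cells, N = 240: λ = 240 × .0625 = 15, df 7 and 232, power .807.

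Both figures reproduce. The sample size is not at fault on this point; N = 240 is used below.

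**2. Algebra.** Code need (V), amount (A) and caring as ±1, so match M = V·A. Let P be own preference, centred. "Participants are automatically and randomly assigned to 1 of 12 conditions, or interventions, (1:1 ratio"), so P is independent of V and A. Suppose recall responds only to the participant's own match: Y = δ·A·P + error. In a balanced design each effect is proportional to the mean product of its term with Y:
- Match, with or without P as covariate: E[V·A · A·P] = E[V]·E[P] = 0.
- Match × preference: E[V·A·P · A·P] = E[V]·E[P²] = 0.
- Amount × preference: E[A·P · A·P] = E[P²], which recovers δ.

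**3. Simulation.** N = 240 (8 × 30), 4,000 runs, residual SD 1, preference split in two at 50/50, amount effect differing by 1.0 SD between preference groups, preference main effect 0.3, no video-match effect. All effect values and the split are assumptions.

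| Term | Mean estimate | Mean SE | Rejected |
|---|---|---|---|
| Match, unadjusted | 0.004 | 0.134 | 5.0% |
| Match, preference as covariate | 0.004 | 0.133 | 5.1% |
| Match (collapsed) × preference | 0.002 | 0.268 | 5.1% |
| Amount × preference | 1.00 | 0.26 | 96.8% |

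With a true video-match effect of 0.5 added, the match estimate was 0.503 both with and without the covariate. Adjustment changed neither the estimate nor its meaning.

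**4. What RQ3 could pick up.** With continuous preference, amount coded ±1 and slope .20, preference × the four tailoring groups (3 df) rejects about 73% of the time at N = 240. The formula agrees: λ = 240 × .04 = 9.6, df 3 and 232, power .73. Only collapsing to match/mismatch brings this down to about 5%.

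**5. Power of the named term.** With amount ±1 and preference in SD units, λ = 240 × slope²:
- slope .10: λ = 2.4, power .34 by formula, about 32% simulated
- slope .15: λ = 5.4, power .64, about 62% simulated
- slope .20: λ = 9.6, power .87, about 86% simulated

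With ±1 coding, a slope of .20 means that the difference between high and low amount changes by 0.40 SD per SD of preference.

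If preferences cluster, power falls. For a two-way split with share p and a difference D in the amount effect, λ = 240·p(1−p)·D²/4:

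| Share p | D = 1.0 SD | D = 0.5 SD |
|---|---|---|
| 50% | .97 | .49 |
| 80% | .87 | .34 |
| 90% | .64 | .21 |

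**The case against.** **RQ3 may already cover it.** A reader might infer that the planned analysis is blind to participant-level tailoring. The document does not support that. Need and amount are separate factors in Trial Design, and the Tailoring subsection distinguishes four kinds of match and mismatch. The preference item sits among the personality traits, which RQ3 lists as moderators. If those factors stay separate, or tailoring keeps four levels, moderation by preference contains the amount × preference term (step 4). What stands is narrower: the term is nowhere named, the coding for RQ3 is not stated, and a collapsed match/mismatch factor would miss it.

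**Place and genre.** The sentence is a permissive remark in a Discussion, and an article may leave individual model terms to a fuller plan. That excuses missing detail. It does not excuse a remedy that is stated and cannot do what is claimed.

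**H2 as operationalised.** A reader might also infer that a null H2 would be a false negative. It would not be. Participants are asked to imagine being the video patient, tailoring is defined at that patient's level, and the limitation is disclosed. A null on that contrast correctly answers the question it poses. The 5% rejection in step 3 follows from simulating no such effect; it shows that adjustment is irrelevant, not that H2 is badly tested.

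**The replacement has limits.** Preference is measured, not randomised, so its interaction with amount may partly reflect correlated traits such as coping style or health literacy. It is one 5-point item whose distribution the document does not give. This limits the status of the added analysis, not the error in the claim.

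**Conclusion.** The point holds in limited form. That covariate adjustment cannot overcome the problem follows from randomisation and needs no assumed effect size. The term that addresses it uses variables already in the design and the survey, and is compatible with RQ3, but is not specified.

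The power figures are conditional. They assume N = 240, residual SD 1, and either a well-spread preference with the stated slopes or the stated splits. On those assumptions the analysis detects large differences and has modest or poor power for smaller ones, so a null on it would not be informative. It should supplement H2 as a secondary or exploratory analysis and not replace it.

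**What to change.** 1. In Strengths and Limitations, remove the claim that controlling for own preference overcomes the issue. Say that adjustment can improve precision or correct chance imbalance only.
2. Label the need × amount contrast that tests H2 as observed tailoring to the video patient.
3. Name amount × own preference, using the full 5-point score and with need and amount kept as separate factors, in the experiment 2 model as a secondary or exploratory analysis of participant-level congruence. State that preference is measured, not randomised, so the term shows effect modification. Report its estimate with a confidence interval and the distribution of the item.
4. Date the addition before analysis. The Results section says data collection is complete and first analyses are still to come; if outcomes have already been examined, label it post hoc.

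The cost is one model term on an item already collected and a few rewritten sentences. No further data are needed.
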